#### Aim #2

Examine aspects of organizational readiness to change that facilitate or deter implementation of patient interventions to improve quality of colonoscopy

To accomplish aim #2, we will identify aspects of readiness to change (i.e., evidence, context, facilitation) associated with implementation (i.e., fidelity, dose, cost), patient (i.e., experience, attendance, adherence), and colonoscopy quality outcomes (aim #1) using structured surveys.

### Subjects

We will recruit physician teams and patient-level subjects for aim #2. The physician team will include physicians recruited for aim #1 and their staff who provide pre-colonoscopy education to patients. We anticipate recruiting a total of 56 physician teams (70 physicians total*0.80 participation) with at least two staff respondents per physician team (56*2 = 112 staff). The study coordinator will send an email to physician team members including a link to an online survey and invitation to participate. The survey invitation will include a personal online code that physician team members can use to complete the online survey. To boost the response rate above, initial mailings will include contacts from our strategic partners, and study staff will follow up weekly with email reminders and phone calls to non-respondents.

### Measures

We will measure both implementation and patient outcomes for aim #2. Implementation outcomes include fidelity, dose, and cost. Fidelity will be measured as the percent of intervention activities delivered as planned with regard to receipt of the tailored patient education material that was provided to sites in the toolkit group. We will use methods published by Rex et al. to measure the cost of care [12]. The estimate will be based on the cost of the initial examination and assumptions about the first round of surveillance taking into consideration the adequacy of bowel preparation at the initial exam, clinical guidelines for surveillance, and Medicare charges for colonoscopy [10]. Patient outcomes include experience, attendance, and adherence. We will use an abbreviated version of the Ambulatory Care Experiences Survey (ACES), a validated survey that measures patients’ experience with a specific physician’s service including perceptions of health promotion support (2 items), service access (4 items), care coordination (2 items), and office staff interactions (2 items) [44]. Patient experience will be a composite score of these scales measured as a continuous variable. We will measure the context, facilitation, and evidence components of organizational readiness to change using an instrument administered to physician teams. Evidence will be measured using 8 items to assess the relative advantage and compatibility of the split-dose bowel preparation and low-literacy patient education interventions. Cronbach’s alpha for reliability of the evidence scale is 0.89 [45]. Sample items from this scale will ask physicians and staff their perceptions about whether using split-dose bowel preparation and low-literacy education with teach-back “is effective based on scientific evidence” and “takes into consideration the needs of patients.” These items will be measured on a Likert-type scale, with response options ranging from 1 = strongly disagree to 5 = strongly agree, and an “I don’t know/Not applicable” option. The context and facilitation components of organizational readiness to change will be assessed through a measure of quality of leader-member exchange (LMX) [32]. Staff will indicate the extent to which each item characterizes their exchange relationships with their supervisors. Sample items will include “How well does your supervisor understand your job problems and needs?” (1 = not at all, to 5 = fully) and “How would you characterize your working relationship with your supervisor?” (1 = extremely ineffective, to 5 = extremely effective).

### Google Analytics measures

To understand how the staff support website is used, we will leverage data tracked and analyzed via Google Analytics. As part of our pragmatic study, endoscopy staff members have flexibility in how they interact with the web-enhanced implementation toolkit. It is, therefore, particularly important to use rigorous yet unobtrusive measurements of staff website use. These data will serve as 1) an intervention check to assess whether or not staff members are using the website as intended and 2) an exploratory measure of website usability and usefulness that will inform future versions of the web-enhanced implementation toolkit. We will assess aggregated data on a number of use indicators, including sessions (i.e., period of time a user is actively engaged with the website), unique users (i.e., first-time users during the selected date range), pages per session, average session duration, average time per page, and website flow (i.e., illustration of the range of website interaction patterns). These data will also help inform qualitative assessment of the acceptability of the web-enhanced implementation toolkit. For instance, short session durations, low usage patterns for certain pages, and intended website flow behaviors will prompt targeted interview questions to expand on these initial quantitative findings.

### Analysis

If we find group-level effects, then we will dichotomize the readiness to change variables at mid-point (high, low) for the sample and analyze readiness to change at the physician-team level. We will examine the distribution of responses to the patient-experience survey for respondents overall and stratified by attendance. Our primary analysis for aim #2 will examine associations between each implementation and patient outcome and readiness to change using linear or logistic generalized estimating equations, depending on the distribution of the outcome, adjusted for patient and procedure characteristics. All analyses will be performed using SAS version 9.2. In addition, we will summarize data from aim #2 as six endoscopy setting case studies based on variability of clinical quality outcomes (aim #1) [46]. If we identify significant relationships between aspects of readiness to change and implementation, patient, or colonoscopy quality outcomes, then we will develop plans to analyze the patterns of these relations in a subsequent study that will be powered to address questions about pathways to readiness to change.

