### Present study

The Strategies to Improve Colonoscopy (STIC) study compares the effect of two implementation strategies, physician education alone versus physician education *plus* an implementation toolkit for staff (i.e., education, website, tailored patient education materials, and a brief consultation), on adoption of three EBPs to improve pre-procedure quality measures (patient experience, adequacy of bowel preparation) and intra-procedure quality measures (cecal intubation, adenoma detection). The EBPs are as follows: 1) split-dosing of bowel preparation, 2) low-literacy education, and 3) teach-back. The goal of the physician education is to improve perceptions of the EBPs and to motivate change among physicians [33], whereas the goal of the implementation toolkit is to improve perceptions of the EBPs, motivate change, and *enable change* among staff [30]. The toolkit will assist endoscopy staff to implement the three EBPs to improve education for bowel preparation for patients. The implementation toolkit contains 1) staff education module, 2) a website containing tools to support staff in learning teach-back and providing low-literacy education materials for patients, 3) patient education materials including a 5-month supply of printed patient education brochures tailored to their site and bowel preparation preferences, and a laminated pocket card and poster to remind and help staff to use teach-back, and 4) a brief consultation with study staff to determine how the EBPs can be integrated into the existing workflow. Education alone is a weak strategy to change physician behavior [34, 35], and there is limited evidence on the effect of implementation toolkits on staff implementation of EBPs. Therefore, the STIC study aims to test the effect of physician education versus physician education plus an implementation toolkit for staff on the implementation and quality outcomes. In light of several adaptations made to the implementation plan and the intentional flexibility in the delivery of the EBPs, this study utilizes a pragmatic study to balance external validity with demonstrated effectiveness of the implementation strategies.

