### Measures

The Center for Clinical Excellence at BJC will obtain all data required for aim #1 from clinical and administrative systems at the endoscopy settings. The primary outcomes for aim #1 are adoption of EBPs, adequacy of bowel preparation, and adenoma detection. We will measure adoption of the EBPs (i.e., split-dosing, use of low-literacy education materials, teach-back) using a structured survey administered to staff and patients at baseline and follow-up. Sample questions on adoption will assess whether staff asked patients to “take half of the bowel preparation medication” (the day before/the morning of the test), with response options including “No,” “Yes,” and “I don’t know/Not applicable.” Questions will also be asked about whether or not staff provided the recommended low-literacy paper instructions and whether or not staff asked patients to “repeat instructions for bowel preparation in their own words.” Both clinical outcomes (adequacy of bowel preparation, adenoma detection) are standard elements of colonoscopy reports [10], and earlier research suggests that these data are routinely recorded in electronic records [39]. Bowel preparation is commonly described using the Aronchick scale (Kappa ICC 0.77) [40] as excellent, good, fair, or poor. Excellent or good ratings are considered adequate [5, 39]. Excellent refers to no or minimal solid stool and only small amounts of clear fluid requiring suctioning. Good refers to no or minimal solid stool with large amounts of clear fluid requiring suctioning. Fair refers to collections of semisolid debris that are cleared with difficulty. Poor refers to solid or semisolid debris that cannot be effectively cleared. We will also capture information about factors that are associated with adequacy of bowel preparation and adenoma detection including characteristics of the patient (age, gender, type of insurance, co-morbid conditions (i.e., history of constipation, diabetes), body mass index, use of narcotic medications) [41], primary language [14], and procedure (i.e., physician specialty, type of bowel preparation, indication for procedure, date of procedure [8]).

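### If group-level effects are found, aim 2 cuts readiness at a sample-dependent mid-point, which wastes information from about 56 teams; its stated adjustment set also omits study group, a potential confounder

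*Protocol article*

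**What the plan says.** The rule is in the Protocol article, Aim #2, Analysis. It is conditional: should group-level effects appear, the plan is to "dichotomize the readiness to change variables at mid-point (high, low) for the sample and analyze readiness to change at the physician-team level". Neither the trigger (group-level effects) nor the mid-point is defined.

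The next step is the primary aim 2 analysis, which relates readiness to each implementation and patient outcome "using linear or logistic generalized estimating equations, depending on the distribution of the outcome, adjusted for patient and procedure characteristics". The aim 1 Measures section lists those characteristics. The patient list covers items such as age, insurance and comorbidity, and the other list is "procedure (i.e., physician specialty, type of bowel preparation, indication for procedure, date of procedure". Study group is in neither.

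The number of units is given under Aim #2, Subjects: "We anticipate recruiting a total of 56 physician teams (70 physicians total*0.80 participation". Two or more staff are expected to respond for each team, 112 in all.

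The aim 2 Measures section describes graded scores. Evidence is an eight-item scale scored 1 to 5 with a reported alpha of 0.89. Context and facilitation are measured by leader-member exchange (LMX) items, with sample items also scored 1 to 5. In the same section, patient experience is kept continuous.

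On the toolkit, the Present study section says "the goal of the implementation toolkit is to improve perceptions of the EBPs, motivate change".

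**The concern.** There are two separate issues.

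**The split.** Once the trigger is met, multi-item scores are reduced to two categories at a point set by whoever happens to be in the sample. A team called high here could be low in another set of endoscopy units, so the result does not transfer. The step is also unnecessary: a team-level analysis needs one score per team, and a mean provides it. With only about 56 teams there is little information to spare.

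**The adjustment set.** The toolkit is meant to improve perceptions of the practices, which the evidence scale measures, and also to improve the outcomes. Assignment is not described as random: it uses baseline bowel-preparation adequacy, patient-unit balance and the physician-staff structure. If readiness is surveyed after the toolkit begins, a readiness-outcome association could partly reflect which group a team was in.

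The article makes significant associations the condition for planning a follow-on study. Lost power can wrongly prevent that step, and an unadjusted group difference can wrongly prompt it.

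**Working it through.** **Reproducing the plan's figures.** 70 × 0.80 = 56 teams and 56 × 2 = 112 staff. Both agree with the article. It states no aim 2 effect size, correlation or power, so what follows rests on stated assumptions.

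**Information kept after a split.** For a normal score linearly related to the outcome, split so that a proportion p lies on one side, relative efficiency is φ(z_p)² / [p(1 − p)].

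- Median split: 0.3989² / 0.25 = 2/π = 0.637. The loss is 36.3%.
- Equivalent teams: 56 × 0.637 = 35.7. Split teams needed to match 56 unsplit: 56 / 0.637 = 88.
- Uneven splits: the loss is 38% at 60/40, 42% at 70/30 and 51% at 80/20.

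**Power, as an illustration.** Fisher z for a team-level correlation r, n = 56, two-sided 0.05: power ≈ Φ(atanh(r)·√53 − 1.96). A median split multiplies r by √0.637 = 0.798.

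- r = 0.37, continuous: 0.388 × 7.280 − 1.96 = 0.87, so power is 81%.
- Same r, split: 0.37 × 0.798 = 0.295; 0.304 × 7.280 − 1.96 = 0.26, so power is 60%.

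| Assumed r | Continuous | Median split |
|---|---|---|
| 0.30 | 62% | 43% |
| 0.37 | 81% | 60% |
| 0.40 | 87% | 67% |
| 0.50 | 98% | 87% |

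A simulation of 8,000 runs at r = 0.367 gave 81% against 60%; the formula gives 80% and 59% there.

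**Omitting study group, as an illustration.** Simulation with 28 against 28 teams, no true readiness effect, a median split, and assumed shifts by study group in readiness and in outcome (SD units; 4,000 runs each):

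| Shift in readiness / outcome | Bias, no group term | Type I error, no group term |
|---|---|---|
| 0 / 0.5 | 0.00 | 5.1% |
| 0.25 / 0.25 | 0.02 | 5.1% |
| 0.5 / 0.5 | 0.09 | 5.8% |
| 0.8 / 0.5 | 0.15 | 9.1% |
| 0.8 / 0.8 | 0.25 | 13.9% |

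With a group term, bias is about 0 and type I error is 4.8% to 5.5% throughout. The problem is negligible for small shifts and absent if group does not move readiness.

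**Consistency within the article.** The aim 1 adoption model includes a study-group term; the aim 2 model as described does not.

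**The case against.** **The split is conditional.** A reader might infer that aim 2 always dichotomises. The text does not support that: the rule applies only if group-level effects are found, and the GEE sentence does not say readiness is binary. This stands, but the condition does not justify the split. If the trigger means clustering of responses within teams, averaging is enough. If it means study-group effects, the split is triggered exactly when group matters, and group is still missing from the stated model.

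**Confounding is not shown.** A reader might also infer that study group does confound the aim 2 results. The article does not establish this, for several reasons:

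- It does not state when the readiness survey is given. Readiness measured at baseline cannot have been changed by the toolkit.
- The toolkit's stated goal bears on perceptions, hence on the evidence scale. Nothing says it aims to change LMX.
- Physician education, which has the same goal for perceptions, goes to both groups and narrows the contrast.
- Fidelity refers to material given to toolkit sites. If it is measured only there, study group cannot confound it.

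All of this stands, so the word is potential.

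**A short phrase in an article is not a full covariate list.** This is fair, and omission alone would not be a finding. But the article does state an adjustment set and define its contents, and procedure date, which is listed, captures calendar time without separating the groups.

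**The power figures do not describe the planned GEE.** Correct. They use a simple correlation at an assumed value and show only the scale of the loss.

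**Aim 2 is formative.** Also correct: the article calls it formative and defers powering to a later study. No aim 1 conclusion depends on it.

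**Conclusion.** The concern holds in a limited form. When its trigger is met, the plan replaces graded readiness scores with a sample-dependent high/low split. For a normal score, a linear association and a median split, this discards about 36% of the information, so 56 teams count as about 36. Because the mid-point is undefined, an uneven split is possible and would lose more. The fall in power from about 81% to 60% applies at an assumed correlation of 0.37 and two-sided 0.05; neither value is given for aim 2.

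The stated adjustment set leaves out study group. This is a potential confounder, mainly for the evidence scale and only if readiness is measured after the toolkit starts. Its size cannot be derived from the article: in the illustration it ranges from nothing to a type I error of about 14%, depending on assumed shifts. The reach of both issues is the aim 2 associations and the decision to plan a follow-on study.

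**What to change.** In Aim #2, Analysis:

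- Enter team-mean evidence and LMX scores as continuous terms in the GEE, for example per SD, whether or not group-level effects are found. Keep high/low for tables and figures only.
- Define what counts as a group-level effect and, for display, what the mid-point is.
- For outcomes measured in both groups, add study group and time-varying toolkit exposure. A fixed group label is not enough, because Table 2 gives group 1 the toolkit in the third segment.
- State when readiness is measured. If a pre-toolkit measurement is already collected, use it as the exposure.

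The model and definition changes take a few sentences and need no further patients or data. The last item differs: the article specifies baseline and follow-up surveys for adoption but not for readiness, so requiring a pre-toolkit readiness survey could mean new data collection. It is therefore recommended only where the data already exist.

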### Dissemination

We will disseminate study findings to scientific and practice stakeholders through manuscripts, presentations, and lay reports. We will also consult with our strategic partners to create physician-level reports that present colonoscopy quality outcomes compared to peers and quality goals. We will also adapt the implementation toolkit based on information gathered from follow-up surveys to improve its usefulness for ongoing support after the study is over and for use in a subsequent study that will examine wide dissemination of the toolkit to outpatient colonoscopy settings based on lessons learned.

### Ethical approval

Our study was found to be in compliance with the Helsinki Declaration and was approved by the Institutional Review Board (IRB) at Washington University’s Human Research Protection Office (IRB ID#: 201401089).

## Discussion

This study will uniquely test the effectiveness of two implementation strategies (physician education versus physician education plus an implementation toolkit for staff) in delivering three bundled EBPs (split-dosing of bowel preparation, low-literacy education, and teach-back) within a pragmatic study. Implementation challenges have already motivated several adaptations to the original plan, reflecting the nature of implementation in real-world healthcare settings. The pragmatic study responds to the evolving needs of its healthcare partners and allows for flexibility in intervention delivery, thereby informing clinical decision-making in real-world settings. Additionally, this comparative-effectiveness study accelerates the translation of research to practice by simultaneously informing stakeholders about the relative advantage of interventions and the strategic processes associated with successful implementation of the interventions. The current study will provide information about what works (effectiveness of the interventions), for whom it works (effectiveness for patients with Medicaid versus other insurance), in which contexts it works (aspects of the setting that influence implementation), and how it works best (physician education versus physician education plus staff training and support).

Additional potential challenges remain, including non-participation in the study. Therefore, we have taken steps to ensure maximum participation by engaging strategic partners in recruitment of physician teams and by planning multiple follow-ups with non-responders to the surveys. To minimize missing data, the research coordinator will check for missing responses as surveys are returned and contact respondents to clarify missing answers when key variables or more than 10 % of the data is missing. The validity of practice-based measures is further strengthened by triangulation of data sources [47–49]. For example, we measure fidelity and dose from physician team and patient perspectives, respectively, to learn about completion of intervention activities from multiple perspectives. This triangulation with multiple methods will add to the robustness and trustworthiness of the findings [49, 50], and when conflicts arise between findings from different sources, it will stimulate us to gather additional data to enhance understanding of the successful implementation processes.

## Consent

Written informed consent was obtained from participants for the publication of this report and any accompanying images.
